## Abstract

**Background:**

The World Health Organization predicts that by 2030 internalising problems (e.g. depression and anxiety) will be second only to HIV/AIDS in international burden of disease. Internalising problems affect 1 in 7 school aged children, impacting on peer relations, school engagement, and later mental health, relationships and employment. The development of early childhood prevention for internalising problems is in its infancy. The current study follows two successful 'efficacy' trials of a parenting group intervention to reduce internalising disorders in temperamentally inhibited preschool children. *Cool Little Kids *is a population-level randomised trial to determine the impacts of systematically screening preschoolers for inhibition then offering a parenting group intervention, on child internalising problems and economic costs at school entry.

**Methods/Design:**

This randomised trial will be conducted within the preschool service system, attended by more than 95% of Australian children in the year before starting school. In early 2011, preschool services in four local government areas in Melbourne, Australia, will distribute the screening tool. The ≈16% (n≈500) with temperamental inhibition will enter the trial. Intervention parents will be offered *Cool Little Kids*, a 6-session group program in the local community, focusing on ways to develop their child's bravery skills by reducing overprotective parenting interactions. Outcomes one and two years post-baseline will comprise child internalising diagnoses and symptoms, parenting interactions, and parent wellbeing. An economic evaluation (cost-consequences framework) will compare incremental differences in costs of the intervention versus control children to incremental differences in outcomes, from a societal perspective. Analyses will use the intention-to-treat principle, using logistic and linear regression models (binary and continuous outcomes respectively) to compare outcomes between the trial arms.

**Discussion:**

This trial addresses gaps for internalising problems identified in the 2004 World Health Organization Prevention of Mental Disorders report. If effective and cost-effective, the intervention could readily be applied at a population level. Governments consider mental health to be a priority, enhancing the likelihood that an effective early prevention program would be adopted in Australia and internationally.

**Trial Registration:**

ISRCTN: ISRCTN30996662

**RCH Human Research Ethics Approval:**

30105A

## Background

Few people in modern societies are untouched by internalising problems, a broad term that refers to emotional distress and encompasses the spectrum of emotional symptoms of anxiety and depression. Although in clinical practice anxiety and depression disorders are seen as multiple, distinct diagnoses, empirical evidence shows high overlap between them and supports use of the broad term internalising problems [1,2]. The World Health Organization (WHO) predicts that, by 2030, internalising problems will be second only to HIV/AIDS in burden of disease [3].

Mental health problems affect 1 in 7 school aged children [4], although they can occur in children of all ages. Internalising (emotional) and externalising (behavioural) problems are among the most common difficulties of early childhood, affecting approximately 15% of those aged 18 months to 5 years [5-8]. Australian community studies have recently confirmed this high prevalence and stability of internalising symptoms across early to mid childhood (e.g. Pearson r's = .53 to .63) [9,10]. By the time internalising disorders are detected problems can be severe and treatment effectiveness can be limited [11,12].

Early internalising problems often have longer-term consequences, with many adult problems having early roots in childhood [4,13,14]. Convergent evidence from prospective and retrospective studies confirms that internalising problems often persist into adolescence and then into adulthood [4,15-24]. Their impacts extend beyond mental health to adult relationships, employment opportunities, and even early mortality. For example, in the British National Child Development Study (N = 11,142), internalising problems at ages 7-11 years were predictive of higher mortality by age 45 (OR 1.20, 95% CI 1.06-1.35) [21].

Evidence suggests that early intervention is key to producing a positive impact because it may be more difficult to influence developmental outcomes later in childhood [25,26]. Though limited, the evidence also supports the cost-effectiveness of intervening early in development [25,27,28]. While emotional functioning continues to develop into adulthood, the early years constitute a window of opportunity for effective mental health promotion in at-risk children. The application of prevention to internalising problems in early childhood is still in its infancy [29]. In 2009, [name] and colleagues conducted a systematic review of early interventions (age 0-8 years) to improve child mental health. This review found a paucity of randomised controlled trials aiming to reduce internalising problems in community settings [30].

### Rationale for the proposed *Cool Little Kids *population-level study

The strongest precursor of internalising problems in young children is temperamental inhibition, manifested as fearfulness and a tendency to withdraw from new situations [29,31-34]. Additional known risks are harsh and overprotective parenting, and parent internalising problems [9,10,34-39]. Together, these account for up to 45% of the variance in early childhood internalising symptoms [9,10,35].

The only randomised trials testing a parenting prevention model in inhibited preschool children were conducted by [name]. [name]'s *Cool Little Kids *program is the first (and, thus far, only) effective early childhood prevention program for internalising disorders [30,40-42]. Targeting child inhibition and overprotective parenting, this parenting program aims to help preschool children become resilient to situational fears and abstract distressing worries. It teaches parents strategies to modify their preschool child's fear and distress, as well as their own (if relevant), based on standard principles for treating internalising disorders in children and adults [11,42].

Two successful efficacy trials of the *Cool Little Kids *program have been reported. [name]'s first trial [41] recruited 146 children aged 4 years with temperamental inhibition, measured by parent-report questionnaire (>85th percentile) and intensive laboratory observation. Intervention parents received a university-based prevention program from teams of two clinical psychologists offering six group sessions designed to reduce overprotective parenting in response to early fearful behaviour. By age 5 years, the intervention children had developed significantly fewer anxiety disorders than controls (50% vs. 64%). These effects were even larger by age 7 (40% vs. 69%) [42]. [name]'s second study [40] recruited 71 inhibited preschoolers whose parents themselves had internalising disorders. The intervention group received an eight-session version of the program which extended to focus on parent anxiety as well as overprotective parenting. Six months later, the intervention children had substantially fewer internalising disorders, diagnosed in only 53% of the intervention group compared to 93% of controls.

[name]'s two efficacy trials are at the cutting edge of prevention research and have major potential public health implications. Population conclusions, however, are precluded by their sample bias (university location and self-selection by advertisement) and the labour-intensive laboratory observation methods used for selection. The unaddressed challenge is to determine 'real world' effectiveness across an entire population. We report the protocol for the next step - to conduct a population-level translational randomised trial.

### Aims and hypotheses

The aims of this trial are to (a) determine the balance of benefits and harms of systematically screening preschoolers for temperamental inhibition and of a parenting intervention program offered to those at risk, (b) examine the impacts on child internalising problems at school entry, and (c) evaluate cost-effectiveness.

We hypothesise that children whose parents enter the program will do better one and two years after baseline (the first two years of school for most) than 'usual care' control children on the outcomes: i) fewer children with internalising disorders, ii) lower mean scores on early child internalising symptoms, iii) lower mean scores on harsh and overprotective parenting, iv) lower mean scores on parent internalising problems. We anticipate that the prevention program will be acceptable and cost-effective.

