### Recruitment and participants

Extending *Cool Little Kids *to a population randomised trial requires more than evidence supporting intervention effectiveness. It requires 1) a universal service system attended by all or almost all 4 year olds, and 2) an acceptable screening tool to systematically identify the children at risk. Primary health care settings were not considered to be an appropriate setting for this screening, because in many countries health practitioners lack the time and resources to screen for this type of problem. In Australia, preschool services are accessed by almost all 4 year olds (95%) [45], at a time when parents and early childhood teachers are concerned about children's impending readiness for school [46]. Brief universal screening can therefore be reliably placed in the preschool setting. The known risk factors for internalising problems are child temperamental inhibition, parents' own internalising problems and overprotective and harsh discipline parenting. The potential benefit versus harm of screening will therefore be considered. For preschool children, it is likely to be more acceptable both to parents and the educational preschool setting to screen inhibition as a child precursor of internalising problems, rather than their parents' mental health and parenting characteristics.

Preschool services from four government areas will be selected to span the sociodemographic spectrum. Written and verbal briefing (study aims, recruiting procedure) will be delivered to preschools across local government areas in the second half of 2010. Recruitment will take place in early 2011 over the first few months of the preschool year. Preschools will distribute a study package including an Information Statement with a screening and consent questionnaire to all parents of children enrolled in their year prior to school. Parents will return this screening and consent questionnaire in a confidential envelope to a sealed letter box at their child's preschool. The questionnaire includes The Short Temperament Scales [47] to screen for child temperamental inhibition (see Table 1) and demographic items.

**Table 1 T1:** Measures used in analysis of study outcomes

Construct	Measure	Administration time points	Number of items	Additional Information

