### Selection criteria

#### Inclusion criteria

Parents will be eligible for the universal screening component of the study (completing the brief parent-report questionnaire) if their child is enrolled for their preschool year (i.e. the year prior to school) at a participating preschool/kindergarten service. They will be eligible to join the trial if the child scores ≥85^th ^percentile on the inhibition subscale of the Short Temperament Scales [47].

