### Allocation

After recruitment and consent, the statistician will coordinate a concealed web-based randomisation process. Computer-generated sequences of random numbers will be used to determine the trial arm status of each child. A block randomisation process, stratified for each preschool separately, will minimise the imbalance between the numbers of intervention and control participants within each preschool. After families are randomised, the study team will notify all parents by letter whether they are in the intervention or control arm, and arrange group session bookings for intervention parents. Participant allocation will be concealed to the clinician assessing diagnostic outcomes; however, the group facilitators and parents cannot be blinded to their group allocation.

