#### Process - Control group

Families in the control arm will receive usual teaching and care from their preschool, early childhood and health services in the community. This may include advice on children's behaviour, but would not include a structured, evidence-based parenting program for temperamental inhibition or internalising problems.

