### Process evaluation

Parents and group facilitators will also be mailed questionnaires at the end of the intervention (late 2011) to evaluate the screening process and intervention, where applicable. All parents will report on perceived harms and benefits of screening. Intervention parents and group facilitators will report on intervention acceptability, extent to which components were implemented, and barriers to attendance. Group facilitators will complete a standard content checklist after each group session to record the degree to which the intervention was delivered. In addition, a research assistant will observe a random 10% of parent groups and evaluate protocol adherence using the content checklist.

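### Both arms are screened before randomisation, so the trial estimates the effect of offering the programme to screen-positive families and cannot determine the benefits and harms of screening

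*Protocol article*

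**What the plan says.** **The claims.** Under Aims and hypotheses, aim (a) is to "determine the balance of benefits and harms of systematically screening preschoolers for temperamental inhibition" and to do the same for the parenting programme. The Background of the Abstract says the trial will "determine the impacts of systematically screening preschoolers for inhibition then offering a parenting group intervention, on child internalising problems and economic costs at school entry". The Discussion lists screening (item a) separately from the programme (item b), and regards wide rollout as warranted if the programme works at population level.

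**The design.** Recruitment and participants: "Preschools will distribute a study package including an Information Statement with a screening and consent questionnaire to all parents of children enrolled". Inclusion criteria: "They will be eligible to join the trial if the child scores" at or above the 85th percentile of the inhibition subscale. All eligible parents are then mailed the trial documents and telephoned, while parents of lower-scoring children get a letter. Allocation: "After recruitment and consent, the statistician will coordinate a concealed web-based randomisation process". Control group: "Families in the control arm will receive usual teaching and care from their preschool, early childhood and health services in the community".

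**What is collected on screening.** Process evaluation: "All parents will report on perceived harms and benefits of screening". Table 1 lists perceptions of the screening process under acceptability, and the Strengths & Difficulties Questionnaire (SDQ) at screening.

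**The economic comparison.** The Methods/Design part of the Abstract says it "will compare incremental differences in costs of the intervention versus control children to incremental differences in outcomes". Economic Evaluation names the control group as comparator for the incremental cost-effectiveness ratio (ICER).

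**The concern.** A screening effect needs a comparison between screened and unscreened children, and none is described. Anything that screening does by itself, such as labelling a child, alerting a parent or prompting help-seeking, happens in both arms and drops out of the difference between them. A positive trial could still be cited as randomised evidence for universal screening, because that is how the aim is worded.

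The economic comparison has a related weakness. Screening is a cost that a targeted programme would incur in routine use, but the stated comparator has been screened too. If screening is charged equally to both arms, or left out, the ICER contains none of it. The evaluation is meant to tell governments whether a publicly funded programme is good value, so the treatment of this cost should be explicit.

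**Working it through.** **1. The plan's own figure.** Inputs from Sample size: 64% against 50%, 80% power, 5% level, up to 20% loss. Two-sided testing and 1:1 allocation are assumed, as neither is stated. The normal-approximation formula for two proportions, without continuity correction, gives 196 per arm, or 392 in total. Then 392/(1 − 0.20) = 490, against the stated figure of around 500. With 200 per arm retained, power is 81.0%. The sample size reproduces, and it is sized for the contrast between offer and no offer. Nothing below changes it.

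**2. What each contrast would need.**
- *Offer versus no offer among screen-positive families*: both groups screened, one offered the programme. This is what is randomised, and what Data analyses compares.
- *Screening versus no screening*: needs an unscreened group. None is described.
- *Screening plus offer versus no screening*: needs an unscreened usual-care group, and outcomes in screen-negative children as well. The control group is screened usual care, and no later outcome assessment is described for screen-negative children.

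The four hypotheses under Aims and hypotheses all concern programme against usual care. None concerns screening.

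**3. What is available on screening.** There are parent-perceived harms and benefits, the SDQ at screening, the screening yield, and the disorder rate in screen-positive children under usual care (the control arm). All are useful, but none is a controlled estimate of what screening does. The article does not make clear whether the parents who report on screening include those of screen-negative children.

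**4. Scale of screening.** Inputs: about 16% positive and about 500 enrolled (Abstract, Methods/Design).
- Children screened: 500/0.16 = 3,125.
- Screen-negative, outside the randomised comparison: 3,125 − 500 = 2,625.
- Screens per positive child: 1/0.16 = 6.25.

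**5. Screening cost in the ICER.** Let c be the cost of one screen, which the article does not give.
- Charged equally to both arms: 6.25c − 6.25c = 0.
- Charged to the intervention arm only: 6.25c per child offered the programme.
- At the planned 14-point reduction, 1/0.14 = 7.14 children are offered the programme per disorder averted, so 6.25 × 7.14 = 44.6 screens per disorder averted.
- Purely for illustration, c of 5, 10 or 20 currency units gives 31.25, 62.5 or 125 per child offered, and about 223, 446 or 893 per disorder averted. A smaller effect raises the latter figures in proportion.

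**The case against.** The best defence is that the aim covers screening and programme together, that the hypotheses claim nothing about a randomised screening effect, and that the process evaluation supplies a method for the screening part. On this view the overreach lies mostly in the verb. That is partly fair: the screening aim is not left without data, and a reader who inferred that it was would be wrong. But the Abstract claims an impact of screening plus offer on child outcomes and costs, and the Discussion lists screening as a separate thing to be determined. Perceptions gathered without a comparison group cannot deliver either.

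On costs, a reader might infer that screening costs are left out and that the ICER is therefore biased in the programme's favour. The article does not support that. Economic Evaluation includes costs broadly and excludes only research, design, set-up and materials development. It does not say how screening is charged, and such detail is commonly left to a fuller plan. It also describes population modelling as feasible, which could bring screening costs in, and its primary framework is a cost-consequence analysis, not a single ratio. What stands is conditional: with the comparator as stated, the costs cancel if they are charged equally or omitted.

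It is also fair to object to replacing the trial-arm ICER with one against no screening. That ratio would combine added screening costs with outcomes from screened controls, and so would assume that screening alone changes nothing. It belongs beside the trial-arm ratio, with the assumption stated. The telephone call should not be counted as a cost of screening all children either, because it goes only to eligible parents and serves to explain trial procedures.

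**Conclusion.** The point holds as a mismatch between the stated aim and the contrast that the design identifies. The trial gives a valid randomised estimate of the effect of offering the programme to screen-positive families. It cannot determine the benefits and harms of screening, or of screening plus offer against no screening.

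The economic part holds conditionally. Screening amounts to about 6.25 screens per child offered, or about 45 per disorder averted at the planned effect, and it nets to zero in a plain comparison of the arms. The screen counts rest on the expected 16% positive rate, and the count per disorder averted also on the 14-point effect taken from the efficacy trial. The money figures are illustrative only. Without a unit cost for screening, or a programme cost to set it against, the documents do not show whether the amount would matter to a decision. The randomised analyses and the sample size need no change.

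**What to change.** 1. In the Abstract, Aims and hypotheses, and Discussion, restate the aim as the effect of offering the programme to screen-positive children, together with a descriptive account of parent-perceived harms and benefits of screening. Do not present a positive result as randomised evidence for screening.
2. In Economic Evaluation, state how screening costs are charged. Keep the trial-arm ICER, and report beside it one that adds to the intervention arm the cost of about 6.25 screens per child offered. Use the observed ratio of screens to positives, and leave out calls made only for the trial. State the assumption that screening alone changes neither outcomes nor service use.

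The cost is rewording, a log of what the screening round consumes, and one further ratio. The downside is a narrower aim and a somewhat less favourable second ICER.

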## Methods/Design

### Overview of Methods

Figure 1 summarises the time line of the trial. It shows graphically the features at each stage that are common to both the intervention and control groups, and unique to the intervention group, in the manner suggested by Perera *et al*. [43].

**Figure 1 F1:**
[figure not shown]
**Graphical depiction of components of the trial**.

*Cool Little Kids *is prospectively registered with an international clinical trials registry (ISRCTN30996662), will be conducted in line with ISPOR guidelines for cost-effectiveness trials alongside RCTs [44], and reported in accordance with the CONSORT statement. Project approval has been obtained from the Ethics in Human Research Committee of the Royal Children's Hospital, Melbourne, Australia

### Recruitment and participants

Extending *Cool Little Kids *to a population randomised trial requires more than evidence supporting intervention effectiveness. It requires 1) a universal service system attended by all or almost all 4 year olds, and 2) an acceptable screening tool to systematically identify the children at risk. Primary health care settings were not considered to be an appropriate setting for this screening, because in many countries health practitioners lack the time and resources to screen for this type of problem. In Australia, preschool services are accessed by almost all 4 year olds (95%) [45], at a time when parents and early childhood teachers are concerned about children's impending readiness for school [46]. Brief universal screening can therefore be reliably placed in the preschool setting. The known risk factors for internalising problems are child temperamental inhibition, parents' own internalising problems and overprotective and harsh discipline parenting. The potential benefit versus harm of screening will therefore be considered. For preschool children, it is likely to be more acceptable both to parents and the educational preschool setting to screen inhibition as a child precursor of internalising problems, rather than their parents' mental health and parenting characteristics.

Preschool services from four government areas will be selected to span the sociodemographic spectrum. Written and verbal briefing (study aims, recruiting procedure) will be delivered to preschools across local government areas in the second half of 2010. Recruitment will take place in early 2011 over the first few months of the preschool year. Preschools will distribute a study package including an Information Statement with a screening and consent questionnaire to all parents of children enrolled in their year prior to school. Parents will return this screening and consent questionnaire in a confidential envelope to a sealed letter box at their child's preschool. The questionnaire includes The Short Temperament Scales [47] to screen for child temperamental inhibition (see Table 1) and demographic items.

**Table 1 T1:** Measures used in analysis of study outcomes

Construct	Measure	Administration time points	Number of items	Additional Information
